#### ‘As-needed’ technical assistance

The purveyor (DW) will initiate individual sessions by videoconference at points when the fidelity alarm bell is triggered by unacceptable drift in one or more behavioral fidelity indices (i.e., R:Q, %OQ, %CR). The alarm will be calibrated using process control benchmarking, with interventionist performances compared against index distributions of research therapists from efficacy trials. For each fidelity index, these distributions will specify an a priori lower control limit to reflect the poorest acceptable TMCU fidelity. Interventionist performances that breach such limits will trigger the alarm, prompting ‘as-needed’ remediation. Technical assistance activities will mirror those of ‘gold-standard’ sessions (i.e., conceptual review, purveyor demonstration, interventionist behavioral rehearsal).

#### Student outcome assessments

The trial coordinator will govern procedures for these assessments at 3- and 6-month follow-up points, for which the purpose is to evaluate TMCU’s clinical effectiveness. Students will similarly complete follow-up web-based assessments on encrypted internet server. Attrition will be minimized through use of extensive contact/locator information by research staff, who maintain networking relationships with local social service agencies. Similar procedures have led to 90+% retention rates in prior TMCU trials.

#### Purveyor/interventionists time-logs

To inform eventual cost analyses, the purveyor and interventionists submit weekly time-logs during the 24-month implementation period. The purveyor documents effort in fidelity-monitoring, individual/group technical assistance, and crisis consultation or other interventionist support activities. The TMCU interventionists document effort recruiting students, delivering TMCU sessions, and attending technical assistance sessions.

The final EPIS phase addresses potential sustainment of TMCU at participating schools. This includes biannual outcome assessments completed by TMCU interventionists, cost-benefit and cost-effectiveness analyses, and elicitation interviews with school leadership.

#### Training outcome assessments

All interventionists complete biannual training outcome assessments (i.e., 6-, 12-, 18-, and 24-months after training). Like preceding assessments, each involves completion of an audio-recorded SP interaction to measure TMCU fidelity, and web-based survey assessment of TMCU knowledge, attitudes, and adoption readiness. A novel component of these follow-up assessments is the inclusion of interventionist-reported satisfaction with technical assistance they receive.

#### Exit interviews

At conclusion of 24-month implementation, two investigative team members (AL, DW) will conduct an elicitation interview with leaders and interventionists at each school. Setting facilitators and barriers to TMCU sustainment will be explored. Like initial interviews with school leadership, exit interviews will be audio-recorded and subject to conventional and directed content analysis [70].

#### Cost analyses

Examination of the value and relative affordability of the two technical assistance conditions will be governed by an investigative team member (KM) with expertise in economic evaluation. This involves use of a standardized survey [74] to estimate annual TMCU costs, incorporating student case-flow data (i.e., average daily student census, number of TMCU sessions delivered) to determine annual cost per student. In comparing costs of the technical assistance methods, data will correspond to aggregate resource use associated with TMCU implementation—including incremental costs associated with each method. Cost analyses will be framed from the school perspective, thus research costs will be excluded. Final products of the analysis will be estimates of total TMCU cost, respective incremental costs of each technical assistance method, annual cost per student, and average cost per TMCU intervention (based on mean number of TMCU sessions completed).

Cost estimates will then be linked with key outcomes to determine cost-benefit and cost-effectiveness. Cost-effectiveness analysis compares differences in the incremental cost of TMCU to differences in its incremental effectiveness in reducing marijuana use to calculate the incremental cost-effectiveness ratio. This ratio describes the additional cost to achieve a unit of desired outcome (i.e., cost per one fewer day of student marijuana use) in TMCU relative to waitlist/control. Cost-benefit analysis broadens the economic impact assessment by comparing intervention costs to the monetary value of reducing negative consequences (i.e., school absences, criminal activity, medical costs, and lost productivity among parents/caregivers. Monetary conversion factors for units of outcome (e.g., cost per criminal offense or cost per day missed from work) translate such outcomes into dollars, which can then be directly compared to intervention costs. The cost-benefit ratio expresses the dollars of benefit generated per dollar invested in the intervention.

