### Hypothesis testing and analytic approach

Hypotheses focus on comparative utility of two technical assistance methods on implementation outcomes among TMCU interventionists and intervention effectiveness among students. Hypothesized effects are that the (1) longitudinal effects of interventionists receiving ‘gold-standard’ vs. ‘as-needed’ technical assistance will not differ, with the latter method proving more cost-beneficial and cost-effective; and (2) effects of technical assistance method for intervention impact on student marijuana use frequency will not differ, with greater reduction expected of students randomly assigned to TMCU vs. waitlist/control.

Trial analyses will be governed by an investigative team member (KK), experienced as a biostatistician and methodologist in adolescent health research. Given nesting of trial data (i.e., repeated observations of students, nested in interventionist caseloads; interventionists nested in schools), multilevel models will include progressive taxonomies in model-building. Initially, an unconditional model will estimate variance of random effects, and a subsequent unconditional growth model will identify the appropriate shape of and variability in rate of change over time for hypotheses involving repeated measures. Technical assistance condition will then be included in conditional models with predictors, with relevant covariates added to determine robustness of main effects and relative goodness-of-fit for each successive model via likelihood ratio tests and deviance statistics. Power analyses (.80, *p* < .05) inform proposed recruitment of (1) 30 interventionists to detect longitudinal effects of training and technical assistance consistent with those for other lay counselors (Cohen’s *d* = 1.00); and (2) 250 students to detect small intervention effects (Cohen’s *d* = .35) relative to waitlist/control.

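### The cost ratios as defined do not contrast the two technical assistance methods, and the benefit ratio sets school costs against benefits that mostly fall outside the school

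*Protocol article*

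**What the plan says.** In the Protocol article, Hypothesis testing and analytic approach, the first hypothesis compares 'gold-standard' with 'as-needed' technical assistance. It expects no difference in longitudinal effects, "with the latter method proving more cost-beneficial and cost-effective". The second hypothesis expects no difference between the methods in the intervention's impact on student marijuana use.

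The Cost analyses section opens with a matching purpose: "Examination of the value and relative affordability of the two technical assistance conditions". Its products include "respective incremental costs of each technical assistance method". It then says: "Cost estimates will then be linked with key outcomes to determine cost-benefit and cost-effectiveness". When it defines the cost-effectiveness analysis, it says that this "compares differences in the incremental cost of TMCU to differences in its incremental effectiveness in reducing marijuana use", and it gives the ratio's meaning as "i.e., cost per one fewer day of student marijuana use) in TMCU relative to waitlist/control". The cost-benefit ratio is defined as monetised benefit for each dollar spent on the intervention, with no comparison of methods.

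On perspective, the same section states: "Cost analyses will be framed from the school perspective, thus research costs will be excluded". The negative consequences to be valued are "school absences, criminal activity, medical costs, and lost productivity among parents/caregivers".

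The Abstract (Methods) and the closing paragraph of the Background's section on process control benchmarking word the economic expectation more narrowly: 'as-needed' assistance should cost less. The Background places this among other expectations, after the co-primary aims on implementation outcomes and intervention effectiveness.

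**The concern.** There are two mismatches, both between things the article states.

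**Contrast.** The hypothesis concerns one assistance method against the other. The only incremental ratio with a named comparator concerns TMCU against waitlist. Whether TMCU is worth its cost and which support method is worth more are different questions, and an answer to the first does not answer the second. A report that followed the definitions could give a favourable TMCU ratio and a lower cost for 'as-needed', and then claim better cost-effectiveness without having combined cost and effect between methods.

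**Perspective.** If costs are those borne by the school and benefits are those enjoyed by anyone, the ratio belongs to no single payer. A school leader could take it as a return to the school, which it is not. For a wider audience it may be incomplete on the cost side. Affordability for schools is central to the trial's rationale, so this reader matters.

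**Working it through.** The article gives no cost, cost-effectiveness ratio or benefit ratio, so there is no figure to reproduce. The check sets definitions against the hypothesis and then illustrates the consequence with assumed values.

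**1. Which contrast each output addresses**

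| Output (Cost analyses) | Contrast | Cost | Effect or benefit |
|---|---|---|---|
| Incremental cost of each assistance method | Between methods | Yes | No |
| Cost per one fewer day of use | TMCU vs waitlist | Yes | Yes |
| Benefit per dollar | None between methods | Yes | Yes |
| Needed for the hypothesis | 'As-needed' vs 'gold-standard' | Yes | Yes |

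No defined output matches the last row.

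**2. What a TMCU-versus-waitlist ratio shows about the methods (all values assumed)**

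Let C be cost per student and E days of use avoided, both relative to waitlist, for 'as-needed' (A) and 'gold-standard' (G), with equal numbers per method. Take C_A/C_G as 100/300, 200/200 or 300/100, and E_A/E_G as 3/3, 2/4 or 4/2.

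- Pooled ratio = [(C_A + C_G)/2] / [(E_A + E_G)/2] = 200/3 = 66.7 in all nine combinations.
- Between-method quantities: ΔC = C_A − C_G, ΔE = E_A − E_G, ratio ΔC/ΔE, and incremental net benefit INB = v·ΔE − ΔC, where v is the value of one day avoided.

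Six of the nine combinations:

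| C_A/C_G | E_A/E_G | Pooled | A vs waitlist | G vs waitlist | ΔC | ΔE | ΔC/ΔE | INB for A |
|---|---|---|---|---|---|---|---|---|
| 100/300 | 3/3 | 66.7 | 33.3 | 100.0 | −200 | 0 | undefined | 200 |
| 100/300 | 2/4 | 66.7 | 50.0 | 75.0 | −200 | −2 | 100 | 200 − 2v |
| 100/300 | 4/2 | 66.7 | 25.0 | 150.0 | −200 | +2 | −100 | 200 + 2v |
| 200/200 | 3/3 | 66.7 | 66.7 | 66.7 | 0 | 0 | undefined | 0 |
| 300/100 | 2/4 | 66.7 | 150.0 | 25.0 | +200 | −2 | −100 | −200 − 2v |
| 300/100 | 4/2 | 66.7 | 75.0 | 50.0 | +200 | +2 | 100 | 2v − 200 |

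Three things follow.

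- The pooled ratio carries no information on which method is better.
- Comparing method-specific ratios against waitlist is not enough either. In the second row 'as-needed' has the lower ratio (50.0 against 75.0), yet at v = 150 its net benefit is 200 − 300 = −100, which favours 'gold-standard'.
- A between-method ratio is also a poor summary. It is undefined when effects are equal, which is what the trial expects. The value −100 appears both where 'as-needed' is cheaper and better (third row) and where it is dearer and worse (fifth row). Net benefit separates these cases.

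**3. Perspective in the benefit ratio (all values assumed)**

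Take school cost 200, school benefit 50 and outside benefit B.

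- Mixed ratio as defined = (50 + B)/200: 0.25 for B = 0, 2.0 for B = 350, 3.0 for B = 550.
- School costs against school benefits = 50/200 = 0.25 for every B.
- Wider costs against wider benefits, with B = 350 and non-school cost K = 400/(200 + K): 2.0, 1.33, 1.0 and 0.8 for K = 0, 100, 200 and 300.

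The ratio can cross 1 on perspective alone. The mixed ratio agrees with the school ratio only if there is no outside benefit, and with the wider ratio only if there is no non-school cost.

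**The case against.** The strongest reply on the contrast is that the Cost analyses section opens with the two assistance methods, plans method-specific incremental costs, and then says cost estimates will be linked with outcomes. On that reading the between-method comparison is unnamed, not excluded. If costs and effects are estimated by method against waitlist, the between-method increments follow by subtraction, and the article does not say the methods will be pooled. If student outcomes do not differ, as hypothesised, the cost difference is what matters, and it is planned. The narrower wording in the Abstract and Background is tested directly by it.

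Much of this stands. A reader might infer that the economic question cannot be answered at all, that cost and effect are never linked between methods, or that a primary hypothesis is untestable. The documents do not support that. The cost half is covered, the time-logs and student outcomes would allow the comparison, and the Background lists cost outside the co-primary aims. What remains is that the sentence defining the ratio fixes waitlist as comparator, while the hypothesis section claims more than lesser cost.

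On perspective, the article presents cost-benefit analysis as a widening of the assessment and never says the benefits return to the school. School absences may also be a school-side benefit. This limits the point but does not remove it: the widening reaches only the benefit side, and no wider cost perspective is stated. A reader might also infer that purveyor effort is left out of costs. The documents do not say so. Purveyor time-logs are collected for the cost analyses, and only research costs are expressly excluded.

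Finally, the choice of estimator and interval can reasonably sit in an unseen analysis plan. The contrast and the perspective cannot be left there, because the article has already stated them and they do not agree.

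**Conclusion.** The point holds as a mismatch in stated contrast and perspective. The ratios as defined do not test the claim that 'as-needed' assistance is more cost-beneficial and cost-effective than 'gold-standard'; only costs are compared between methods. The benefit-per-dollar ratio mixes school costs with benefits that mostly fall elsewhere, so it cannot be read as a return to schools.

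The size is unknown. Every monetary value in the working is assumed and shows the mechanism only. A reader might take 2.0 against 0.25 as an estimate of how far the ratio is inflated, but the article offers no figure that would support one. The uninformative 66.7 rests on pooling the methods in equal numbers, which the article neither states nor rules out. The fidelity and clinical comparisons are not affected.

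**What to change.** 1. **Name the contrast.** In Cost analyses, state 'as-needed' versus 'gold-standard' as the test of the economic hypothesis: the cost difference together with the difference in days of use, expressed as incremental net benefit over a range of values per day avoided. The interval should respect interventionists as the randomised unit, for example by resampling interventionists. Keep TMCU versus waitlist as a separate analysis. Alternatively, limit the hypothesis section to the lesser-cost expectation of the Abstract and Background, which the planned cost comparison can answer.

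2. **Match perspectives.** Report a school-perspective ratio that counts only benefits accruing to schools. Report the wider-benefit ratio separately, labelled as wider than the school, with non-school costs counted where data exist and otherwise stated as omitted.

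**Cost.** The first change needs wording and modest extra analysis; time-logs and student outcomes are already collected. The interval may be wide: 250 × 2/3 ≈ 167 TMCU students over 30 interventionists is about 5.6 each. The school-perspective ratio will look less favourable unless all benefits accrue to schools. A full wider ratio is not clearly cheap, because the article lists no collection of student or family costs.

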### Data management

Trial data consist of audio-recordings and web-based surveys. Audio-recordings include elicitation interviews of school leadership, SP interactions completed by TMCU interventionists, and TMCU sessions with participating students. Web-based surveys are completed by TMCU interventionists, other school-based staff, and students. Upon their collection, audio-recordings will be transported immediately to secure university office space and uploaded as audio-files to a password-protected network and identified by appropriate trial identification number. Original recordings will then be deleted from digital recording devices. Upon their completion, web-based surveys will be stored on encrypted university servers accessible only by trial staff, similarly identified by trial identification number. As outlined in a corresponding Data Safety and Monitoring Plan, linkage between identifying information for trial participants and trial identification numbers will be destroyed at trial conclusion.

Planned reliance on web-based surveys for most of the trial data collection limits the need for data entry procedures. An exception is paper forms corresponding to audio-recording data (i.e., TMCU fidelity ratings), for which numeric data will be entered and later reviewed for verification by separate study staff. Likewise, automated entry of web-based survey data will be reviewed for verification by study staff who will identify and fix anomalies. Record of data anomalies will be maintained in a trial logbook. To facilitate data completeness, a data tree will be established in order that data is analyzed and stored in specific files, backed up in secure locations on a weekly basis.

### Hypothesis testing and analytic approach

Hypotheses focus on comparative utility of two technical assistance methods on implementation outcomes among TMCU interventionists and intervention effectiveness among students. Hypothesized effects are that the (1) longitudinal effects of interventionists receiving ‘gold-standard’ vs. ‘as-needed’ technical assistance will not differ, with the latter method proving more cost-beneficial and cost-effective; and (2) effects of technical assistance method for intervention impact on student marijuana use frequency will not differ, with greater reduction expected of students randomly assigned to TMCU vs. waitlist/control.

Trial analyses will be governed by an investigative team member (KK), experienced as a biostatistician and methodologist in adolescent health research. Given nesting of trial data (i.e., repeated observations of students, nested in interventionist caseloads; interventionists nested in schools), multilevel models will include progressive taxonomies in model-building. Initially, an unconditional model will estimate variance of random effects, and a subsequent unconditional growth model will identify the appropriate shape of and variability in rate of change over time for hypotheses involving repeated measures. Technical assistance condition will then be included in conditional models with predictors, with relevant covariates added to determine robustness of main effects and relative goodness-of-fit for each successive model via likelihood ratio tests and deviance statistics. Power analyses (.80, *p* < .05) inform proposed recruitment of (1) 30 interventionists to detect longitudinal effects of training and technical assistance consistent with those for other lay counselors (Cohen’s *d* = 1.00); and (2) 250 students to detect small intervention effects (Cohen’s *d* = .35) relative to waitlist/control.

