### Units of analysis and measures

Trial measurement includes students nested in interventionist caseloads, which in turn are nested in schools. Units of analysis exist at three levels: school, interventionist, and student. Corresponding data collection instruments are listed in Table 2.

**Table 2 Tab2:** Trial measurement instruments and processes

Unit of analysis	Instrument/process	Respondent(s)	Timing of assessment
Schools			
	Implementation leadership scale [62]	School staff members	Trial outset
	Implementation climate scale [63]	School staff members	Trial outset
	Site visit including elicitation interview with school leadership	Principal, other leaders	Trial outset
	Exit interview	Principal, other Leaders	Trial conclusion
Interventionists			
	Demography and background	Interventionists	Pre-training
	MI knowledge/attitudes test [64]	Interventionists	Pre/post-training + 6-, 12-, 18-, 24-month
	Adoption readiness scale [65]	Interventionists	Pre/post-training + 6-, 12-, 18-, 24-month
	Fidelity-rated interaction with a standardized patient [66]	Interventionists	Pre/post-training + 6-, 12-, 18-, 24-month
	Training satisfaction survey	Interventionists	Post-training
	TA satisfaction survey	Interventionists	6-, 12-, 18-, 24-month
	Interventionist time-log	Interventionists	Weekly, over 24 months
Students			
	Demography and locator data	Students	Baseline
	Normative perceptions [67, 68]	Students	Baseline
	Life goals [69]	Students	Baseline
	Global Appraisal of Independent Needs [70]	Students	Baseline, 3- and 6-month
	Marijuana Problems Scale [71]	Students	Baseline, 3- and 6-month
	Marijuana Motives Measure [72]	Students	Baseline, 3- and 6-month
	Self-efficacy to Avoid Marijuana [73]	Students	Baseline, 3- and 6-month
	Student Academic Self-Report [74]	Students	Baseline, 3- and 6-month
	Student Engagement Instrument [75]	Students	Baseline, 3- and 6-month
Investigators			
	Technical Assistance Time-Log	Purveyor	Weekly, over 24 months
	Stages of Implementation Completion Checklist [76]	Research coordinator	Continual

Trial design proposes recruitment of approximately ten schools, with 2–4 interventionists recruited per participating school to garner an intended sample of TMCU interventionists (*N* = 30) randomized to ‘gold-standard’ or ‘as-needed’ technical assistance conditions; Self-referring students (*N* = 250) will be randomized in a 2:1 ratio to receive the TMCU intervention vs. waitlist/control

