#### Students

Trial measurement of 250 high school students to self-refer for randomization (in 2:1 ratio) to TMCU or waitlist/control includes baseline survey of demography, contact information, normative perceptions of marijuana use [60, 61], and life goals information [62] incorporated as personal feedback. Repeated-measures assessed in intervention outcome assessments (i.e., baseline, 3- and 6-month follow-up) include the following student-report instruments (1) Global Appraisal of Independent Needs [63], offering recent marijuana use and diagnostic symptoms; (2) Marijuana Problems Scale [64]; (3) Marijuana Motives Measure [65]; (4) self-efficacy to avoid marijuana use [66]; (5) Student Academic Self-Report, tapping homework completion, attendance, and disciplinary actions [67]; and (6) Student Engagement Instrument [68], measuring academic and social engagement. This will be supplemented by administrative data accessed from participating school districts. Students will receive financial remuneration to incentivize retention and completion of outcome assessments.

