#### Student recruitment

At each school, TMCU interventionists will contribute to on-site promotion via classroom presentations and cafeteria exhibits. Self-referring students will have a TMCU interventionist read a brief explanation of the trial, and if interested will be directed to a web-based assent/consent form with contact information for university-based research staff. Students will provide informed assent/consent prior to interventionist conduct of a brief, confidential screening interview to determine eligibility. Inclusion criteria are that students be (1) 14–19 years old, (2) enrolled in 9th–12th grade, and (3) active marijuana users (9+ days in prior month). Students will be excluded if they are not fluent in English, have a thought disorder, or refuse to be randomized to condition. Ineligible students will receive standard marijuana resources/referrals.

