#### Student randomization

Upon determination of eligibility, students will be randomized in a 2:1 ratio to TMCU or waitlist/control. This will occur after blocking by student gender and grade-level, independently at each school. The trial seeks 250 student participants during its 24-month period of TMCU implementation.

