#### TMCU delivery

Trained interventionists will deliver the TMCU to eligible, self-referring students over a 24-month period. This consists of two sessions, each 45 min in duration occurring a week apart. The initial session develops rapport, explores aspects of the student’s marijuana use, and identifies sources of motivation to change. The latter session includes conjoint review of the personal feedback report, with the interventionist eliciting self-motivational statements about reduction or discontinuance of marijuana use and offering advice for such changes. Notably, interventionists deliver TMCU to waitlist-assigned students only after a requisite 6-month intervening period.

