#### Hypothesis 1b: comparable clinical effectiveness of technical assistance methods

For student outcomes, multilevel models extend to three levels for repeated observation of marijuana use frequency and secondary outcomes (i.e., problems, motives, perceptions, self-efficacy to abstain, academic performance, and engagement) nested within interventionists. A primary test parameter is the interaction of time × technical assistance method of the TMCU interventionist as a dummy-coded predictor. As temporal effects may not conform to simple linear growth curves, models will test different specifications of time (i.e., piecewise, polynomial, or other nonlinear approaches). The a priori non-inferiority margin (i.e., ½ SD) will again be applied and, if exceeded, a test of superiority will specify the direction and magnitude of differential impact.

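### Students are described as nested in interventionist caseloads, but in the 6-month outcome window this fits only the TMCU arm, so the TMCU-versus-waitlist standard error depends on an unstated coding of waitlist students

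*Protocol article*

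**What the plan says.** The protocol article describes the student data structure twice. Under Units of analysis and measures: "Trial measurement includes students nested in interventionist caseloads, which in turn are nested in schools". Under Hypothesis testing and analytic approach, as the reason for using multilevel models: "repeated observations of students, nested in interventionist caseloads; interventionists nested in schools". The Hypothesis 1b section also places repeated student outcomes within interventionists, in a three-level model. None of these places treats the waitlist arm separately.

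The procedures say something different about that arm. Individual randomization is described as "students will be randomized in a 2:1 ratio to TMCU or waitlist/control". Under TMCU delivery, "interventionists deliver TMCU to waitlist-assigned students only after a requisite 6-month intervening period". The Students section gives the repeated measures as "intervention outcome assessments (i.e., baseline, 3- and 6-month follow-up", so the final outcome falls at 6 months.

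The analytic section hypothesizes a greater reduction in marijuana use with TMCU than with waitlist, and sizes the student sample for that effect (250 students, d = 0.35, power 0.80, p < .05). It gives no model structure for this comparison other than the general nesting statement, and no ICC.

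**The concern.** In the outcome window an interventionist treats TMCU students only. Differences in interventionist skill can therefore make outcomes alike within caseloads in the TMCU arm, with no counterpart from delivery in the waitlist arm. This is a partially nested design, and the article describes it as fully nested.

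The difference matters for the standard error of the between-arm contrast. With one random intercept per interventionist shared by both arms, TMCU minus waitlist becomes a within-cluster comparison and the intercept largely cancels. Real variation that exists in one arm only does not cancel. A model that lets it cancel reports too much precision, and the 5% test of clinical effectiveness rejects too often. Other ways of placing waitlist students at the interventionist level have other consequences, so the validity of the interval depends on a choice that the article does not state.

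**Working it through.** **The plan's own figure.** For d = 0.35, two-sided 5% and power 0.80 at 2:1, the waitlist n is (1.96 + 0.84)² × (1 + 1/2) / 0.35², which rounds up to 97. With 194 TMCU students the total is 291. At 250 students the power is 0.742. So 250 does not reproduce at 2:1 without some unstated gain, such as a baseline correlation of 0.4 (power 0.812). That is a separate matter. What counts here is that the stated calculation shows no design effect and so gives no hint of how the nesting was handled.

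**Inputs.** 250 students at 2:1 give 167 TMCU and 83 waitlist. There are 30 interventionists, so m = 167/30 = 5.57 TMCU students each, and about 10 schools. The ICC in the TMCU arm is an assumption, varied from 0.05 to 0.20. Total outcome variance is set to 1.

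**Formula.**
- Clustering ignored: Var = 1/167 + 1/83 = 0.01804, SE = 0.134.
- Clustering in the TMCU arm only: Var = [1 + (m − 1) × ICC]/167 + 1/83.
- Type I error when the first SE is used and the second is true: 2 × [1 − Φ(1.96 × SE ratio)].

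| Assumed ICC | True SE | SE ratio | Type I error |
|---|---|---|---|
| 0.05 | 0.139 | 0.964 | 5.9% |
| 0.10 | 0.144 | 0.932 | 6.8% |
| 0.20 | 0.153 | 0.876 | 8.6% |

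**Simulation by coding of waitlist students.** 3,000 trials per setting under no effect, with equal caseloads, one outcome per student, REML, Wald z test, school fixed effects and clustering in the TMCU arm only. Monte Carlo error is about 0.4 points at a 5% rate.

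| Coding of waitlist students | ICC 0.02 | ICC 0.05 | ICC 0.10 | ICC 0.20 |
|---|---|---|---|---|
| Nominal interventionist, shared intercept | 4.7% | 6.3% | 8.5% | 10.3% |
| Clusters of one | 4.3% | 5.2% | 6.1% | 5.4% |
| One waitlist cluster per school | 3.6% | 4.4% | 4.2% | 3.0% |
| Partially nested model | 4.4% | 5.4% | 6.5% | 5.8% |

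At ICC 0.05 the mean reported SE against the empirical SD of the estimate is 0.133 against 0.140 (nominal link), 0.140 against 0.140 (clusters of one), 0.150 against 0.140 (pooled by school) and 0.139 against 0.140 (partially nested).

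Without school fixed effects the pattern is the same; the nominal link gives 6.0%, 7.5% and 11.2% at ICC 0.05, 0.10 and 0.20. The partially nested results slightly above 5% come from a z test with 30 clusters, which is why small-sample degrees of freedom belong in the fix.

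**The case against.** The strongest reply is that the article never writes out a model for TMCU versus waitlist. The three-level student model sits under Hypothesis 1b, where "A primary test parameter is the interaction of time × technical assistance method of the TMCU interventionist as a dummy-coded predictor". The Background frames that comparison as use among TMCU-exposed students, and there caseload nesting is correct. On this view the coding of waitlist students is ordinary SAP detail. Part of this stands: the technical assistance comparison is not at fault, and a full protocol or SAP may handle the waitlist arm properly. But the point is not a missing detail. The article states a structure for all students that its own procedures contradict, and that structure is the only one offered for an effect it hypothesizes and powers.

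A reader might infer that the standard error is necessarily too small and that the true type I error exceeds 5%. The documents do not support that. They fix neither the coding nor the ICC, and the second table shows inflation, near-nominal error or conservatism depending on the coding. At ICC 0.05 or below, even the unfavourable coding costs only about one percentage point.

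It would also go too far to say that waitlist students have no interventionist at all. Under Student recruitment, "Students will provide informed assent/consent prior to interventionist conduct of a brief, confidential screening interview to determine eligibility". This gives a nominal link in both arms, and any clustering due to the screener would properly cancel. What is absent in the window is delivery of TMCU. The same link, however, makes the literal reading of the nesting a natural one to program.

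Finally, the simulations use one outcome per student. The plan has repeated measures, so the sizes may not carry over exactly.

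**Conclusion.** The point holds in conditional form. For TMCU versus waitlist, the stated nesting does not describe about 83 of 250 students during the outcome window. Applied literally through a nominal interventionist with a shared intercept, it makes the standard error too small whenever interventionists vary in the TMCU arm, with type I error of about 6% at ICC 0.05 and up to about 10% at 0.20. Pooling waitlist students by school errs the other way, and clusters of one are close to correct. These sizes assume equal caseloads, a single outcome per student and ICC values that the documents do not supply. A nonzero ICC is plausible on the plan's own terms, since it expects interventionists to vary in performance and tests whether their support affects student outcomes. The correction is worth making because it is cheap and removes the dependence on an unstated coding.

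**What to change.** Amend Units of analysis and measures, and Hypothesis testing and analytic approach, to say that only TMCU-assigned students are nested in interventionist caseloads during the 6-month window. For TMCU versus waitlist, specify a partially nested model:

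- an interventionist random effect for TMCU-assigned students only (a random coefficient on the TMCU indicator);
- in growth models, the same restriction on an interventionist-level random time slope, because the contrast of interest is then a difference in change;
- waitlist students entered as clusters of one;
- a separate residual variance in each arm;
- Satterthwaite or Kenward-Roger degrees of freedom.

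The technical assistance model among TMCU-exposed students can stay as it is.

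The cost is analysis wording, with no new data or participants. The confidence interval becomes wider: the formula above gives √(true variance/0.01804) = 1.04, 1.07 and 1.11 at ICC 0.05, 0.10 and 0.15, and the ratio of simulated mean SEs (partially nested to nominal link) is slightly higher, 0.1427/0.1323 = 1.08 at 0.10. Roughly 4% to 12% is a fair range. One assumption remains: the model sets any screener effect among waitlist students to zero, and the plan should say so.
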